Study protocol

The efficacy and dose optimization of sufentanil postoperative patient controlled analgesia after moderate surgery: a single center, randomized, double-blinded trial

Study site: Xi’an Jiaotong University, Second Affiliated Hospital

Responsible Department: department of anesthesiology

Supervisor: [name], [name]

1. Study background

As the “comfort medicine” being developed, pain control rises as a focused issue between patients and physicians. The relief of acute postoperative pain is emphasized among anesthesiologists and surgeons [1-4]. Surgeries injured local tissue, leading to release of histamine and inflammatory factor like bradykinin, prostaglandins, serotonin, and neurotrophic factors etc., which result in the activation of the peripheral nociceptive receptor. The nociceptive signal is transmitted through A δ or C fibers to the dorsal horn of spinal. After serials of complicated modulation, the nociceptive signal is sensed by brain. If the acute pain was not treated properly and in time, the sympathetic nerve system would be stimulated, resulting in increased oxygen consumption of the myocardium, decreased oxygen supply to the myocardium, ultimately increase of perioperative heart ischemia or myocardial infarction. Other harm due to the high tense of sympathetic system is that the recovery of the gastrointestinal function would be delayed, even ileus. Inadequate treatment of the postoperative pain will result in shallow rapid respiration, reluctant to coughing, and eventually increase of the pulmonary complications. It is recognized that lack of postoperative pain control will lead to some undesired influences like the clinic experience of the patients, postoperative rehabilitation, prolonging of the hospital stay, increase of probability of readmission, or even the increased risk of cerebrovascular and cardiovascular events or deaths [5-7]. Besides, if the acute pain was not treated effectively and properly, not only it would severely influence the quality of life, a huge mental distress, but also might develop to chronic pain or neuropathic pain. And it was observed that after surgery, the degree of pain was related to subsequently developed chronic pain [8]. Therefore, in the daily practice o f anesthesia, pain free becomes as our main pursuit.

The management of postoperative pain consists of multiple models and methods. The old ways relied on the intramuscular injection of analgesics by nurses. While the recent decades, the patient controlled analgesia had shown plenty of advantages like effective pain relief, better medical benefits, the participation of patients and satisfaction. The patient controlled intravenous analgesia (PCIA) as one of the main parts of self-analgesia has now become very prevalent during the postoperative period. In the past morphine or fentanyl was used as the main drug for pain control in PCIA. But these two narcotics are inappropriate for continuously infusion because of the pharmacokinetics which might lead to accumulation of drugs and more side effects. And patients would be reluctant to press if the pain was not well relieved. Sufentanil is one of new narcotics deprived of morphine with stronger efficacy and longer duration of effect time. Sufentanil has more stable pharmacokinetics than morphine or fentanyl and more suitable for long duration infusion. Moreover, it has multiple administration routine like intravenous, intranasal, sublingual administration, all of which had been shown safe and effective in postoperative pain control [9-11]. But there are still some deficiencies in the use of sufentanil for postoperative pain like inadequate analgesia which patients complaining of unbearable pain and demanding more analgesics, or over analgesia which results in over sedation or respiratory depression. The dose and efficacy of sufentanil in PCIA is unclear and a proper reference of sufentanil in PCIA is still lacking. Therefore, its very necessary to assess its analgesic effect and ultimately to optimize the use of sufentanil in PCIA. And we conduct this study to observe the use of sufentanil in PCIA after moderate surgery, and to determine the optimal dose of sufentanil with best pain relief and minimal side effects.

1. Study objective

Assess of the analgesic effect of sufentanil in postoperative PCIA and its dose optimization.

1. Study design

A single centered, prospective, randomized, double-blinded trial

1. Study drug

Sufentanil citrate injection, 1ml:50μg, Yichang Humanwell Pharmaceutical Co., Ltd.

Electronic infusion pump, 100ml, Royal Fornia Medical

1. Randomization

The patients are eligible to be randomized provided the surgery duration within 4 hours. The eligible patients will be assigned to one of three treatment arms (A, B, C) through the table of random numbers based block randomization stratified by enrollment sequence. Each block contains 6 patients and there must be 2 patients in each block assigned to A treatment, 2 assigned to B treatment and 2 assigned to C treatment. Fifteen groups of permutation and combinations were combined based on the table of random numbers generated by a statistician. The allocation sequence is according to the sequence of surgery.

1. Blind

The allocation mark is sealed in a sequentially numbered envelope one each till 30 min before the end of surgery. The envelope will be then unsealed by the nurse who is responsible for the preparation of the pump. The observer is another investigator who is blind to the allocation. The nurse and observer must not communicate about the patient’s medication or analgesic effect. The pump has no label on except the enrollment sequence number.

1. Patient population

The patients with no gender limit aging from 20 to 75, BMI 18 to 28 kg/m^2, American Society of Anesthesiologists (ASA) grade I to II, anticipated surgery duration within 4 hours and agreed to sign consent paper are scheduled for selective moderate surgery including abdominal surgery (gastrectomy, colectomy, and rectectomy for cancer). Women participants in the study have to be menopause or use routine contraceptive method.

Patients with known allergy or contradiction to the treatment drugs, or severe respiratory, cardiovascular or neurological disease, hepatic or renal dysfunction, psychiatric history or unstable mental state are excluded from the study. Patients with a history of drug or alcohol abuse, chronic use of opioids and pregnant or breast-feeding will be excluded as well.

1. Study group

The participants are randomly allocated to three groups as following: low dose group (sufentanil 1.5μg/kg), moderate dose group (sufentanil 2.0μg/kg) and high dose group (sufentanil 2.5μg/kg)

1. Anesthesia

Preoperative

All the patients are fasting for 8 hours before surgery and no preoperative medication. After admission in to the operation room, the patient will be supplied with mask oxygen. Then the peripheral venous access will be established. Ringer’s solution will be dropped in to the venous line and vital signs monitored including electrocardiography, blood pressure, saturation of pulse oximeter, bispectral index for anesthesia depth. Record the basal value of the vital signs and bispectral index value.

Induction and maintenance

All patients will receive general anesthesia. The patients receive no premedication. Ten minutes before anesthesia induction a loading dose of dexmedetomidine with 1 μg/kg is infused over 10 minutes. Then anesthesia is induced with midazolam 2 mg, sufentanil 0.5 μg/kg, propofol 1-2 mg/kg. Cisatracurium 0.2 mg/kg is given to facilitate orotracheal intubation with a cuffed tube. Anesthesia will be maintained with continuous infusion of propofol 3-7 mg/kg/h, remifentanil 0.1-0.25 μg/kg/min, cisatracurium 0.1 mg/kg/h and dexmedetomidine 0.2-0.5 μg/kg/h with positive pressure ventilation in a circle system. And the bispectral index (BIS) value will be maintained between 40 and 60. Mean blood pressure (MAP), Heart rate (HR), pulse oxymetry (SpO2%), end-tidal CO2 (ETCO2), blood loss, and transfusion are recorded during anesthesia. Cisatracurium and dexmedetomidine will be discontinued until peritoneum closure, while propofol and remifentanil will be stopped until the last stitch of skin.

Immediately after discontinue of remifentanil, a loading dose of 10μg sufentanil will be infused intravenously, and then the PCA pump will be connected and started. Then 5μg sufentanil will be administrated each 5 minutes if the patient complains of pain till the pain relieved or respiratory rate less than 10 per minutes.

Intraoperative management

Provide a stable hemodynamics. It is defined as hypertension as the blood pressure is 30% higher than the basal value, hypotension as the blood pressure is 30% lower than the basal value. Both situations need treatment. If heart rate less than 50 beats/min or 30% less than the basal value, then treat with 0.06mg/kg atropine intravenously, repeat if necessary. Record all the treatments, causes, drugs, doses and administration ways. Other situation needs treatment should be recorded as well.

Postoperative management

Extubation is according the guideline of management of tracheal extubation (Popat et al. Anaesthesia, 2012, 67, 318-340). Remove the endotracheal tube provided that the patient can open eye on command and simultaneous respiratory recovered as RR>8 beats/min and PETCO2<45 mmHg. Patients will be cared in the post-anesthesia care unit (PACU) for at least 30 min until the discharge criteria was met.

1. Study route

Patient enrolled consecutively, informing consent signed

No premedication. Ten minutes before anesthesia induction a loading dose of dexmedetomidine with 1 μg/kg is infused over 10 minutes. Then anesthesia is induced with midazolam 2 mg, sufentanil 0.5 μg/kg, propofol 1-2 mg/kg cisatracurium 0.2 mg/kg. Anesthesia will be maintained propofol 3-7 mg/kg/h, remifentanil 0.1-0.25 μg/kg/min, cisatracurium 0.1 mg/kg/h and dexmedetomidine 0.2-0.5 μg/kg/h and the bispectral index (BIS) value will be maintained between 40 and 60.

Cisatracurium and dexmedetomidine discontinued until peritoneum closure, propofol and remifentanil until the last stitch of skin. Immediately after discontinue of remifentanil, a loading dose of 10μg sufentanil will be infused intravenously, and then the PCA pump will be connected and started. Then 5μg sufentanil will be administrated each 5 minutes if the patient complains of pain till the pain relieved or respiratory rate less than 10 per minutes. Explain the use of PCA pump to the patients.

Sufentanil 1.5μg/kg + Tropisetron 10mg to 100ml

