The investigators should be relative fixed. Study and discuss the protocol and brochure. Get consensus of opinion in methods of data collection and measurement.

File record

Recorded data in CRF should be traceable from original case, otherwise input in the CRF directly. At the latter circumstance, the CRF will be seen as original data. The data needed checking should be recorded well. Research files and all original data should be conserved well.

1. Statistical analysis

The aim of the study was to determine the optimal dose of sufentanil PCIA after moderate surgery with most pain relief. The expected standard deviation of means was 15 mm h, and standard deviation of subjects was 45 mm h of VAS. The significance level was set at 0.05 and the power at 0.8. Then the calculated sample size was 30 patients each group. Patient characteristic data (height, weight, age, laboratory test data, anesthesia duration, surgery duration, drugs consumptions) were compared by analysis of variance (ANOVA). Patient gender, surgery type were compared by Chi-square analysis. Comparisons of VAS or NRS for pain were performed with repeated-measures ANOVA. Ranked data as sedation degree and vomiting and nausea scale were analyzed with the Kruskal–Wallis tests. Probability values under 0.05 were considered significant.

1. Appendix

Visual analogue scale (VAS) of pain

From no pain (=0) to worst pain imaginable (=10). Patients are encouraged to draw a stroke across the 10 cm line. The distance from “0” to the stroke is record as pain score.

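### Allocation is balanced within 15 consecutive blocks, but the pain analysis names no block term: the dose test turns conservative if pain drifts over enrollment, and a nearly free gain in precision is left unused (minor)

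*Protocol*

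**What the plan says.** The Protocol's Randomization section calls the scheme "block randomization stratified by enrollment sequence". It fixes the block composition: "Each block contains 6 patients and there must be 2 patients in each block assigned to A treatment", and likewise two each for B and C. It also fixes the number of blocks: "Fifteen groups of permutation and combinations were combined based on the table of random numbers". Fifteen blocks of six make 90 patients, which is 30 per arm. Allocation follows the order of surgery, and the Study route section has patients enrolled consecutively, so each block is a short stretch of the enrollment period.

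The Statistical analysis section gives the pain analysis in one sentence: "Comparisons of VAS or NRS for pain were performed with repeated-measures ANOVA". It mentions neither block nor enrollment period. The sample size in the same section rests on three statements: "The expected standard deviation of means was 15 mm h", "standard deviation of subjects was 45 mm h of VAS" and "The significance level was set at 0.05 and the power at 0.8". They lead to "Then the calculated sample size was 30 patients each group". The protocol does not say whether the 45 mm h includes variation over the enrollment period.

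**The concern.** Exact balance within each block means that a shift common to all six patients of a block cancels from every comparison between arms. An ANOVA without block does not use this. It leaves the variation between blocks in the between-patient error, against which dose is tested. The error variance is then larger than the variance that actually affects the arm contrasts, so standard errors are too wide and the test rejects too rarely.

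At stake is efficiency in the main pain comparison. The plan reaches its power target with almost nothing to spare (0.801 at 30 per arm, 0.786 at 29), so avoidable error variance is worth removing when doing so is cheap.

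**Working it through.** **Inputs.** From Statistical analysis: SD of means 15 mm h, SD of subjects 45 mm h, alpha 0.05, power 0.8, 30 per group. From Randomization: 15 blocks of 6, 2:2:2. *Assumed, because the protocol gives no figure:* the share ρ of the total variance that lies between blocks, taken as 0, 5, 10 and 20% and modelled as a linear trend over the 15 blocks.

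**Step 1: reproduce the plan's figure.** In a repeated-measures ANOVA the dose main effect is tested between patients, so one summary value per patient suffices.
- f = 15/45 = 1/3 and λ = 90 × (1/3)² = 10, with 2 and 87 degrees of freedom.
- Noncentral F gives power 0.801 at n = 30 and 0.786 at n = 29. The stated 30 per group is reproduced.
- This reads the SD of means with divisor k = 3. With divisor k − 1 the answer would be 45 per group, so the first reading is evidently the one used.

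**Step 2: cost of a block term without drift.** Error degrees of freedom fall from 87 to 87 − 14 = 73. With λ still 10, power goes from 0.801 to 0.798.

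**Step 3: how far the unblocked error is inflated.** Let σ² be the within-block variance and τ² the variance of the block shifts. The arm means vary only through σ², but the expected unblocked error mean square is σ² + (90/87)τ². With total variance 45² = 2025:

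| ρ | σ² | τ² | Expected unblocked error | Ratio to σ² | Standard error too wide by |
|---|---|---|---|---|---|
| 5% | 1923.75 | 101.25 | 2028.5 | 1.054 | 2.7% |
| 10% | 1822.5 | 202.5 | 2032.0 | 1.115 | 5.6% |
| 20% | 1620 | 405 | 2039.0 | 1.259 | 12.2% |

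The ratio depends only on ρ, so the conservatism is the same whether or not 45 mm h already contains the drift.

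**Step 4: type I error and power.** Results without block are from simulated trials with equally spaced arm means of SD 15. Power with block follows from noncentral F on 2 and 73 degrees of freedom. If 45 is the total SD, λ = 10/(1 − ρ), that is 10.53 / 11.11 / 12.50. If 45 is the within-block SD, λ stays at 10.

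| ρ | Type I error, no block | 45 = total SD: power without / with block | 45 excludes drift: power without / with block |
|---|---|---|---|
| 0 | 0.05 | 0.80 / 0.80 | 0.80 / 0.80 |
| 5% | 0.043 | 0.80 / 0.82 | 0.78 / 0.80 |
| 10% | 0.036 | 0.80 / 0.84 | 0.76 / 0.80 |
| 20% | 0.024 | 0.81 / 0.88 | 0.70 / 0.80 |

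With block in the model, type I error stays at about 0.05 throughout.

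**Step 5: how much drift these shares imply.** For 15 equally spaced values, range/SD = 14/√((15² − 1)/12) = 3.24. If 45 is the total SD, the change from first to last block is 3.24 × 45 × √ρ, or about 33 / 46 / 65 mm h for 5 / 10 / 20%. Under equal spacing the low- and high-dose means are 2 × 15 × √1.5 = 36.7 mm h apart, so even the 5% case is a large trend.

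The block term pays for itself at a share of about 0.5 to 1%: at ρ = 0.5%, λ = 10.05 and power with block is 0.800; at ρ = 1%, λ = 10.10 and it is 0.802. By the same formula, that is a change of about 10 to 15 mm h over the whole enrollment.

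**The case against.** The strongest objection concerns power. A reader might infer that any drift leaves the trial short of its stated 80%. The protocol does not support this. The stated power comes from a one-way calculation without blocks, and the SD that belongs in such a calculation is the ordinary between-patient SD, which already contains variation over time. On that reading the planned test delivers 0.80 to 0.81 in every case shown. A shortfall needs two things that the protocol does not state: that 45 mm h excludes drift, and that drift is large. This objection stands, and it limits the point to power forgone.

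Second, nothing in the protocol suggests drift. There is one centre, a narrow population (ASA I–II, BMI 18–28, surgery within 4 hours), a scripted anaesthetic and a largely fixed team of investigators. This also stands. It makes large drift less plausible without excluding it, so the drift figures are a range of assumptions and no forecast.

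Third, stratification by enrollment order may be only a loose name for ordinary permuted blocks, with no prognostic stratum intended. That is probably right. The 2:2:2 balance is still built in, however, and the effect on the error term does not depend on the name.

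Fourth, the protocol names only the type of ANOVA, and its between-patient terms may be set in an analysis plan that is not shown. Silence here does not prove that blocks will be ignored. This lowers the weight of the point. The suggestion remains useful unless such a plan already contains the term.

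**Conclusion.** The point holds as a minor one. The design balances the arms within 15 consecutive blocks, and the named pain analysis has no term for them. If pain levels change over enrollment, the dose test is conservative, with type I error about 0.043 / 0.036 / 0.024 at assumed block shares of 5 / 10 / 20%. It also forgoes about 2 / 4 / 7 percentage points of power if 45 mm h is the total SD. If 45 mm h excludes drift, power falls below target, to about 0.78 / 0.76 / 0.70.

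The sample size of 30 per group is correct for its stated inputs. There is no bias between arms and no inflation of type I error. All drift figures rest on an assumed linear trend and on one summary value per patient. A block shift that is constant over the assessment times does not enter the within-patient dose-by-time comparison, so the point concerns the overall dose effect.

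**What to change.** In the Statistical analysis section, or in the statistical analysis plan if there is one, add the randomisation block (15 levels) as a between-patient factor in the repeated-measures ANOVA of pain, and test dose against the within-block error (2 and 73 degrees of freedom on a per-patient summary). A statement of whether the 45 mm h is a total or a within-block SD would settle which column of the power table applies.

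This takes one line of wording. The block number follows from the allocation list and the enrollment sequence number, so no new data and no further patients are needed. The downside is 14 error degrees of freedom, which lowers power from 0.801 to 0.798 if there is no drift. The change is best fixed before any pain data are seen by arm. It is an optional gain in efficiency, and the trial remains valid without it.

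### The protocol fixes and prints a constant block size of 6 (2:2:2), so someone who tallies earlier allocations could deduce up to one in five before the envelope is opened

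*Protocol*

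**What the plan says.** The Randomization section describes one list for one centre. It calls the method "block randomization stratified by enrollment sequence", which creates no separate lists. Block size and content are fixed and printed: "Each block contains 6 patients and there must be 2 patients in each block assigned to A treatment", then "2 assigned to B treatment and 2 assigned to C treatment". The number of blocks is given as well: "Fifteen groups of permutation and combinations were combined based on the table of random numbers generated by a statistician". The list is used in theatre order: "The allocation sequence is according to the sequence of surgery".

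The same section makes randomization conditional: "The patients are eligible to be randomized provided the surgery duration within 4 hours". It does not say who applies this condition.

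The Blind section puts each allocation in a sequentially numbered sealed envelope until 30 minutes before the end of surgery. Then: "The envelope will be then unsealed by the nurse who is responsible for the preparation of the pump". The observer is a different person, is blind, and may not discuss the patient's medication or analgesic effect with the nurse. No other communication barrier is stated.

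The Data quality text asks for a fairly stable team of investigators and tells them: "Study and discuss the protocol and brochure". Nothing in the protocol varies the block size, withholds it from site staff, or rotates the person who opens the envelopes.

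**The concern.** Sealed envelopes conceal the next allocation only if it cannot be worked out from the ones already opened. With a constant and published block size, the end of each block can be worked out by anyone who has followed the block from its start. The nurse's role comes closest, because it opens the envelopes in sequence.

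What is at stake is selection. Two things are settled before an envelope is opened: whether the operation meets the 4-hour condition, and which patient comes next in the order of surgery. If someone able to influence either one learned the coming arm, the make-up of the arms could be affected. The protocol bars communication between nurse and observer, but says nothing about communication between the nurse and those who apply the condition or schedule the cases.

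**Working it through.** **Inputs.** Block size 6, content 2:2:2, 15 blocks and one list in order of surgery (Randomization section); 30 patients per group (Study route and Statistical analysis sections).

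**The plan's own totals.** 15 × 6 = 90 = 3 × 30, so the block count and the sample size agree. The stated 30 per group also reproduces. In a one-way ANOVA with three groups and f = 15/45 = 1/3, power at two-sided 0.05 is 0.786 with 29 per group and 0.801 with 30. The block scheme does not affect this.

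**Certain foreknowledge.** A block has 6!/(2!·2!·2!) = 90 equally likely orders. An allocation is certain before opening when only one arm has places left in the block.

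- Positions 1 to 4: never certain, because at least three places remain and no arm has more than two.
- Position 5: certain only if the last two places belong to the same arm. Given the arm of one of them, one of the other five places is in that arm, so the probability is 1/5.
- Position 6: always certain.

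Expected number per block: 1/5 + 1 = 1.2. Share: 1.2/6 = 20%. Over the trial: 15 × 1.2 = 18 of 90.

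**Partial foreknowledge.** The table shows what a person who has seen the whole block so far can do at each position.

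| Position in block | 1 | 2 | 3 | 4 | 5 | 6 | Mean |
|---|---|---|---|---|---|---|---|
| Probability that an arm is already exhausted | 0 | 0 | 0.2 | 0.6 | 1 | 1 | 2.8/6 = 0.467 |
| Probability that the best guess is right | 0.333 | 0.400 | 0.500 | 0.533 | 0.600 | 1.000 | 0.561 |

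The chance rate for a guess is 0.333.

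**Effect of mixed block sizes.** I simulated 90 allocations in blocks of 6 or 9, each size equally likely. The tracker was assumed to know the possible sizes but not their order.

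| Scheme | Certain before opening | Best guess right |
|---|---|---|
| Constant 6 (protocol) | 20% | 56% |
| 6 and 9 mixed at random | about 5% | about 54% |

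Sizes 6 and 9 can still give exactly 90 patients: six blocks of each is 6 × 6 + 6 × 9 = 36 + 54 = 90, with 6 × 2 + 6 × 3 = 30 per arm.

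**The case against.** The strongest reply is that the 20% is a ceiling with no demonstrated route to harm. Most of that stands.

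- **A reader might infer that the nurse actually knows one allocation in five.** The protocol does not establish this. It names a role, not one person, mentions no tally, and directs the investigators, without naming the nurse, to study the protocol. What can be said is that a person who tracks the sequence and knows the size could deduce that share.
- **A reader might infer selection bias.** The nurse's only stated tasks are to open the envelope and prepare the pump. The Study route has patients enrolled consecutively with consent beforehand, and no section lets the nurse admit, defer or reorder patients.
- **A reader might treat the 4-hour condition as a matter of discretion.** The text states a duration limit, which is measurable, and by 30 minutes before the end of surgery the duration is largely settled. What the protocol leaves open is who applies the condition.
- **A reader might think outcome blinding is broken.** The nurse learns every allocation on opening under any block scheme. The observer sees none, so the 20% does not apply to the observer.
- **A reader might think the number on the pump, or one known arm, gives away other arms.** Position alone leaves each arm at 1/3. One known allocation moves another place in the block only to 1/5 for that arm and 2/5 for each of the others.

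It is also fair that mixed sizes barely change the best-guess rate. What the reply does not remove is that the 4-hour condition and the order of surgery precede the opening of the envelope, and that the only stated barrier is between nurse and observer. Concealment therefore rests on conduct where the design could protect it.

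**Conclusion.** The point holds as a minor weakness of concealment. With constant 2:2:2 blocks of 6 disclosed in the protocol, up to 1.2 of 6 allocations (20%, an expected 18 of 90) could be deduced with certainty before opening. At least one arm could be excluded for 47%.

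These figures assume a person, or people sharing a tally, who see all earlier allocations and know the block size. They become bias only if that knowledge reaches and influences whoever applies the 4-hour condition or orders the cases. The protocol neither states nor excludes this, so no size of bias can be calculated. The sample size and the observer's blinding are unaffected, and the protocol's figures on this point are consistent with each other.

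**What to change.** Before first enrolment, or for the envelopes still unused, have the statistician regenerate the list with block sizes mixed at random, for example 6 and 9, keeping 90 patients and 30 per arm. In the protocol given to site staff, replace the sentences on block size and content with a statement that permuted blocks of varying size are used and that the statistician holds the details until database lock.

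The cost is one new list, a new set of envelopes and one changed sentence, with no extra patients or staff. The gain is mainly the removal of certain foreknowledge, from 20% to about 5% even for someone who knows the possible sizes. The downside is a slightly larger possible imbalance between arms if enrolment stops inside a block of 9.
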